### Statistical analyses

The data distributions of normality will be evaluated by the Kolmogorov–Smirnov test. In the case of normal distribution, an analysis of covariance (ANCOVA test) with Tukey’s post hoc will be used to test the differences between groups. The between-group mean difference, 95% confidence interval, and effect size (Cohen’s f) will be reported. The Kruskal–Wallis test will be used for non-normal data distribution, and the effect size will be calculated with Cohen’s r. All participants will be included in the analysis following an intention-to-treat approach.

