**Discussion:**

If the improvements in the outcomes are similar in the two groups, BFR exercise with reduced load and volume may be an interesting alternative in the treatment of knee OA, especially when exercises with high loads generate joint pain.

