### Sample size estimates

It is estimated that a sample size of 32 patients per group would be necessary to test our research hypothesis on the primary outcome (knee pain). The parameters utilized to sample size calculation included an intergroup variability (σ) in the VAS gain of 21% for both groups [44]; a non-inferiority limit (d) of 14%, which is less than the minimum clinically perceptible difference, usually considered to be 15% for the VAS [45]; a type-I error of 5% (α =0.05); a power of 80% (β=0.20) and a dropout rate of 15%.

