## Discussion

This trial will examine whether BFR resistance exercise with very low load and low volume will present effects similar to those of the HIRE on pain, muscular performance, physical function, disease severity, and quality of life in patients with knee OA. Although previous studies have shown positive effects of BRF exercises, the true efficacy of this intervention is hampered by the matching of the total exercise volume compared with HIRE [14]. In addition, no study has evaluated the effects of BFR exercise with very low load (10% of 1-RM) and low volume in patients with knee OA. If effective, BFR exercise with 10% of 1-RM can be an interesting treatment for generating lower joint overload and consequently lesser pain during exercise.

The present study can be considered of high methodological quality because it is randomized and prospectively registered, masks the evaluators and patients, concealed allocation, and used an intention-to-treat approach. Sample size was calculated to provide adequate statistical power to identify possible differences in the study primary outcome. In addition, the 3-month follow-up will enable verification of the persistent effects of BFR exercise in patients with knee OA, thus filling this gap since studies on this topic generally assess the effects only immediately after treatment.

The exercise load will be periodically adjusted, thus maintaining the overload principle of strength training. We will estimate the 1-RM from a submaximal test (7–10 RM test) to minimize the pain interference in the load determination. In addition, to avoid a possible measurement bias (gain strength due to learning with the test and not due to neuromuscular adaptations) we choose to measure the strength in three different ways (isometric, isokinetic and 7-10 RM test). [46]. Another strength of this trial is external validity. In order to enable extrapolation of the study findings to a larger portion of the population, it was decided not to limit the participation of patients according to gender, unilateral or bilateral involvement, and the use (or not) of medications. The randomization will be balanced and the statistical analysis will be adjusted according to these factors to minimize possible confounding factors due to this greater sample coverage.

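### The trial is sized for non-inferiority with a 14% limit, but the named tests are tests of difference and no rule sets the reported interval against that limit

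*Protocol article*

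**What the plan says.** **Sample size estimates (Protocol article).** The primary outcome, knee pain, is sized with "a non-inferiority limit (d) of 14%, which is less than the minimum clinically perceptible difference", an "intergroup variability (σ) in the VAS gain of 21% for both groups", "a type-I error of 5% (α =0.05"), and "a power of 80% (β=0.20) and a dropout rate of 15"%. The result is that "a sample size of 32 patients per group would be necessary". The sidedness of alpha is not stated.

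**Statistical analyses.** For normally distributed data the plan is ANCOVA with Tukey, which "post hoc will be used to test the differences between groups". For non-normal data it is Kruskal–Wallis with effect size r. On the ANCOVA route the between-group mean difference, its 95% confidence interval and Cohen's f are to be reported. The 14% limit does not appear in this section or anywhere else outside the sample size section.

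**Aim and interpretation.** The abstract says: "If the improvements in the outcomes are similar in the two groups, BFR exercise with reduced load and volume may be an interesting alternative". The main Discussion says: "This trial will examine whether BFR resistance exercise with very low load and low volume will present effects similar to those of the HIRE". The same Discussion describes the sample size as chosen to give power for detecting differences, which is not what the sample size section describes.

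**The concern.** The article states two incompatible hypotheses for one primary outcome. The sample size section asks whether BFR is worse than HIRE by less than a fixed limit. The analysis section and the Discussion ask whether the groups differ. The conclusion wanted is similarity, which the article does not define.

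A test of difference cannot establish similarity. Its only contribution to that conclusion is a non-significant p-value, and non-significance becomes easier to obtain as the trial gets smaller. If the result were read that way, a deficit as large as the trial's own limit could go unrecognised at a rate far above the 5% error that the sample size allows.

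**Working it through.** **Inputs.** Margin 14, SD 21, alpha 0.05, power 80%, dropout 15% (Sample size estimates). Three assumptions are needed: 14% and 21% mean 14 mm and 21 mm on the 0–100 mm VAS, because the text speaks of a percentage in VAS gain; the true difference used for sizing is 0; alpha is one-sided.

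**1. Reproducing 32 per group.**

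n = 2 × SD² × (z₁₋α + z₁₋β)² / margin²

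- Non-inferiority, one-sided 0.05: 2 × 21² × (1.645 + 0.842)² / 14² = 27.8 per arm. Then 27.8 × 1.15 = 32.0, the stated figure. Rounding up to 28 and dividing by 0.85 gives 33.
- Non-inferiority, one-sided 0.025: 35.3, so 36 per arm, and 42–43 with dropout.
- Two-sided 0.05 test of a difference of 14: 36 per arm, and 42–43 with dropout.
- Equivalence (two one-sided tests at 0.05): 38.5 per arm, and about 44–46 with dropout.

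Of these, only the one-sided 5% non-inferiority formula gives the stated size. The number evaluable is then 28 from the formula, or 27 from 32 × 0.85 = 27.2.

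**2. Chance of a non-significant two-sided 5% test when BFR is truly worse.** SE = 21 × √(2/n), non-central t with 2n − 2 degrees of freedom. At n = 28 the SE is 5.61.

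| Evaluable per arm | True deficit 14 | True deficit 15 | True deficit 20 |
|---|---|---|---|
| 28 | 31% | 25% | 6% |
| 27 | 33% | 27% | 7% |
| 20 | 46% | 41% | 17% |
| 17 | 53% | 48% | 23% |

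The 20 and 17 rows apply only if 40 patients in total are enrolled, as the abstract and the eligibility section state (20 × 0.85 = 17). A one-sided 5% non-inferiority test would wrongly pass 5% at a true deficit of 14.

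**3. Covariate adjustment.** The article gives no covariate correlation. If covariates explain a share R² of the variance, the residual SD is 21 × √(1 − R²). At 28 per arm and a deficit of 14:

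- R² = 9% (assumed): SD 20.0, non-significant in 27%.
- R² = 25% (assumed): SD 18.2, non-significant in 19%.

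**4. What the reported 95% CI would look like.** At 28 per arm the half-width is 2.005 × 5.61 = 11.25. An observed BFR disadvantage just under 11.25 is non-significant, yet its upper limit is 22.5, well beyond 14. To keep the upper 95% limit below 14, the observed disadvantage must be below 14 − 11.25 = 2.75.

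**5. Power under each confidence level, 28 evaluable per arm, true difference 0.** About 79–80% with a 90% CI (one-sided 0.05) and about 69% with a 95% CI (one-sided 0.025). The reported interval and the sample size therefore use different error rates.

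**The case against.** The strongest reply is that the analysis section does more than test. It reports a mean difference with a 95% CI, which on the ANCOVA route is the quantity needed to judge non-inferiority. A reader might infer that the trial has no means of assessing non-inferiority, and that would go too far. What is missing on that route is a sentence tying the interval to the limit. The Kruskal–Wallis route offers less, since effect size r cannot be set against a VAS margin.

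A reader might also infer that a non-significant p-value will be reported as similarity. The article does not say so: the word is left undefined, and a decision rule could sit in a fuller plan. That reply stands as far as it goes, but the sections shown still conflict, and no other criterion is offered.

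A third tempting reading is that a clearly inferior treatment could be endorsed. The figures do not support it at the calculated size. A deficit of 14 is, in the article's own terms, below the perceptible difference of 15%, and at a deficit of 20 the test misses only 6–7% of the time with 27–28 per arm. The 46–53% figures depend on the separate conflict between 40 patients in total and 32 per group.

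The objection that unadjusted rates are upper-end values for an ANCOVA is also right, and the adjusted range above reflects it.

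**Conclusion.** The contradiction is established from the text alone: a non-inferiority sample size, difference tests, a Discussion that describes power for differences, and no rule linking the reported interval to the limit. It must be resolved, because the primary conclusion depends on it.

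If non-significance were taken as similarity, the false reassurance at a true deficit of 14 would be about 31–33% at the calculated size, or 19–27% with the assumed covariate gain at 28 per arm, against the 5% that the design intends. It would be 46–53% without adjustment if only 40 patients are enrolled. These rates assume the mm reading of the percentages and an SD of 21. The documents do not support saying that the analysis is confined to a p-value, or that a much larger deficit would commonly be missed at the calculated size.

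**What to change.** - State the primary analysis as non-inferiority: the ANCOVA-adjusted BFR minus HIRE difference in VAS at 12 weeks. Declare non-inferiority only if the upper confidence limit lies below the limit, written in mm.
- Match the confidence level to the sample size alpha. A 90% CI keeps 32 per group. If the 95% CI is the criterion, restate power as about 69% at 28 evaluable per arm, or size for 36 evaluable per arm.
- For non-normal data, replace Kruskal–Wallis with an interval on the VAS scale judged by the same rule, for example a bootstrap or Hodges–Lehmann interval.
- State that a non-significant difference will not be called similar.
- Correct the Discussion sentence that describes the sample size as chosen to detect differences.
- Tukey does nothing with two arms; dropping it is only tidying.

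With the 90% CI the cost is wording alone. Keeping the 95% CI costs either the power shown or more patients. Recruitment was under way at submission, so the rule should be fixed before outcome data are seen.

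### A normality pre-test can move the primary outcome to Kruskal–Wallis, a branch that does not use the non-inferiority limit and cannot carry the promised covariate adjustment

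*Protocol article*

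**What the plan says.** Sample size estimates sets up a non-inferiority comparison on the VAS gain, with "a non-inferiority limit (d) of 14" per cent, a standard deviation of 21%, a 5% type-I error, 80% power and 15% dropout.

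Statistical analyses then makes the method depend on a pre-test: "The data distributions of normality will be evaluated by the" Kolmogorov–Smirnov test. There are two branches.

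- **Normality not rejected:** "In the case of normal distribution, an analysis of covariance (ANCOVA test") is used to test for differences. The next sentence adds: "The between-group mean difference, 95% confidence interval, and effect size (Cohen’s f) will be reported".
- **Normality rejected:** a Kruskal–Wallis "test will be used for non-normal data distribution, and the effect size will be calculated" as Cohen's r. Nothing else is listed for this branch.

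No outcome is exempted, so the rule covers the primary outcome. The Discussion, after naming gender, unilateral or bilateral involvement and medication use, says that "the statistical analysis will be adjusted according to these factors".

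**The concern.** The sample size rests on a mean difference compared with a limit. The fallback is a rank test of equal distributions which, with two arms, is equivalent to the Mann–Whitney test, and its only listed effect size has no units. Neither can be set against a limit on the VAS scale. Kruskal–Wallis also takes no covariates, so on that branch the adjustment promised in the Discussion cannot be made.

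The gate is also aimed at the wrong quantity. ANCOVA relies on approximately normal residuals, whereas the pre-test is applied to the data distributions. The outcome data would therefore decide whether the primary result is an adjusted difference with an interval or an unadjusted rank p-value. If the gate fires, the tempting route to a conclusion of similar effects is a non-significant p-value, which is not evidence of non-inferiority.

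**Working it through.** **1. What the sample size was built for.** Inputs from Sample size estimates: limit d = 14, σ = 21, α = 0.05, power 80%, dropout 15%. The article does not say whether α is one- or two-sided; one-sided is tried first. The assumed true difference is 0.

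n per group = 2 × [σ(z₀.₉₅ + z₀.₈₀)/d]² = 2 × [21 × (1.645 + 0.842)/14]² = 27.8, so 28.

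Dropout: 27.82 × 1.15 = 31.99, so 32; or 28/0.85 = 32.9, so 33. The stated 32 per group is reproduced. With one-sided 0.025 the formula gives 36 before dropout and 43 after (36/0.85 = 42.4), which does not match. The design is thus a mean-difference non-inferiority comparison at one-sided 5%.

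**2. What each branch delivers.**

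| | ANCOVA branch | Kruskal–Wallis branch |
|---|---|---|
| Difference on the VAS scale | listed | not listed |
| 95% confidence interval | listed | not listed |
| Effect size | Cohen's f | Cohen's r |
| Can carry covariates | yes | no |
| Output comparable with the limit | yes, through the interval | none |

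**3. What a non-significant Kruskal–Wallis result would mean.** Simulation with normal data, SD 21 mm and a true difference of exactly 14 mm (14% read as 14 points of the 0–100 mm scale, an assumption). Share of trials with p > 0.05:

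- 20 per arm (half of the 40 patients in the Abstract): about 49%
- 28 per arm (the pre-dropout figure from step 1): about 34%

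A valid one-sided 5% non-inferiority test would wrongly succeed in at most 5% of trials at that point.

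**4. How often the gate might fire.** The article does not say whether the Kolmogorov–Smirnov test is corrected for estimated parameters (Lilliefors), or whether it is applied to raw scores or gain, per arm or pooled. Simulations with 20 per arm, latent SD 21, and the switch triggered by rejection in either arm:

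| Quantity tested | Latent post-treatment mean | Lilliefors-corrected | Uncorrected |
|---|---|---|---|
| Raw VAS floored at 0 | 10 mm (32% at floor) | about 84% | about 10% |
| Raw VAS floored at 0 | 20 mm | about 29% | about 0.3% |
| Raw VAS floored at 0 | 30 mm | about 11% | 0% |
| VAS gain (assumed baseline 55 mm, r = 0.5) | 10, 20 or 30 mm | about 8–11% | about 0% |

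Two independent 5% tests reject in 1 − 0.95² = 9.75% of trials under perfect normality. Values near 10% in the corrected column are therefore false alarms, not evidence of skew.

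**The case against.** Four points on the other side carry weight.

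- **The switch may be rare.** A reader might infer that most trials of this kind would fall into the rank branch. The document does not support that. The high rates need a corrected test, raw scores and a mean close to the floor. No expected VAS mean is given, eligibility requires at least moderate disease, and pain is also measured during a chair stand test. If gain is tested, the rate is about the false-alarm rate or nil. This stands: no single switch rate can be claimed.
- **The gate is not the only obstacle.** A reader might infer that the trial as a whole cannot answer its non-inferiority question because of this rule. That goes too far. The problem described here is confined to the fallback branch. The ANCOVA branch is also worded as a test of differences, so deleting the gate would not by itself supply a non-inferiority test; but that branch does yield an interval that can be held against the limit.
- **The sentence on mean difference and interval might cover both branches.** It is not expressly restricted. But it pairs them with Cohen's f, directly follows ANCOVA and comes before a fallback that has its own effect size. Even on the generous reading, the fallback test takes no covariates and does not test the limit.
- **An analysis plan not shown could settle details.** That is true of interval methods and sensitivity analyses. The gate, the fallback test and its effect size are stated outright in the article, so this is a rule fixed badly and not an omission.

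Loss of adjustment for baseline pain should not be counted as a broken promise: the article does not name baseline VAS as a covariate.

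**Conclusion.** The point holds for the fallback branch. The stated rule lets the data select, for the primary outcome, a test that does not use the 14% limit, cannot be adjusted as the Discussion promises and, on the natural reading, comes with no difference or interval on the VAS scale. If non-significance on that branch were read as similarity, a treatment worse by exactly the limit would pass in about 49% of trials at 20 per arm or 34% at 28, against at most 5% for a valid test. Those figures assume normal data, SD 21 mm and a limit of 14 mm. The arm sizes are shown as a range because the article gives both 40 patients in total and 32 per group.

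The likelihood of the switch is unsettled, from 0% to about 84% across the assumptions tried. The defect does not depend on that rate: whenever the gate fires, the non-inferiority question has no planned answer. This should be corrected; it does not invalidate the design.

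**What to change.** For the primary outcome, delete the normality gate. State that ANCOVA, with the factors named in the Discussion (gender, unilateral or bilateral involvement, medication use), is the primary analysis in all cases. State also that the confidence interval for the adjusted mean difference will be compared with the non-inferiority limit. Check residuals rather than raw distributions; if they are clearly non-normal, use a bootstrap or heteroscedasticity-robust interval for the same adjusted difference. Report the rank test with a Hodges–Lehmann interval as a sensitivity analysis only.

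The cost is revised wording and a little extra analysis work. No additional data or patients are needed for this change.

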### Inclusion and exclusion criteria

A total of 40 men and women with unilateral or bilateral knee OA diagnosed according to the American College of Rheumatology criteria will be considered eligible if they:are at least 50 years of age;are in the postmenopausal period (for women);are between 1.50 and 1.75 m in height;have a body mass index between 18.5 and 35 kg/m^2^;have moderate to very severe knee OA (score between 5 and 13 on the Lequesne Questionnaire);have a score of at least 24 on the Mini-Mental State Examination;do not have peripheral vascular disease, systolic blood pressure greater than 160 or less than 100 mm Hg, diastolic blood pressure greater than 100 mm Hg, deep vein thrombosis, diabetes, history of myocardial infarction, stroke in the previous year, or history of cancer that has generated limitations to exercise;do not have other orthopedic/neurological diseases that affect gait and do not present any other inflammatory myoarticular disease;have not undergone surgery or any invasive procedure on the knees in the previous 6 months;have not participated in physiotherapeutic treatment or lower-limb strengthening programs in the past 3 months;are not practicing regular physical activity (two or more times per week) for lower limbs (except for those who only practice walking).

Participants will be excluded if they:experience pain that completely prevents them from performing the exercises proposed by two consecutive or three non-consecutive sessions or refuse to remain in the study;begin taking specific medications that are for OA or that interfere with study outcomes;begin to exercise or perform other treatment modalities for knee OA after initiating treatment.

Patients will be able to maintain treatment with stable doses of anti-inflammatory or other medications of regular use in the 3 months prior to the start of the study [15, 23] but should avoid using medications on evaluation days. Subjects who discontinue participation in the study will be invited to participate in the assessments 3 months after the start of treatment, and 6 months after the randomization. Thus, all individuals will be included in the intention-to-treat analysis. Therapists who deliver the intervention will be eligible if they have undergone specific training for the treatment protocol.

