### Intervention

The intervention will consist of two weekly sessions with about 60 min of duration each during 12 weeks for a total of 24 sessions. The volunteers will be re-evaluated after 12 weeks and from then on will be guided to practice exercises according to their own volition [20]. In both groups, the sessions will be started with 5 min of light-intensity warm-up on a stationary bike. All subjects included will be instructed not to initiate regular exercises beyond treatment sessions [8, 18]. Both groups will perform bilateral strengthening of the thigh muscles through squatting exercises on the hack machine (angle between 0° and 60° of knee flexion) and leg extension exercises (angle between 90° and 45° of knee flexion) [11, 20]. These amplitudes of movement were selected to minimize the load of the patellofemoral joint during the exercises [24].

In addition to exercises to strengthen the thigh muscles, trunk, hip, and calf exercises will be performed for both groups. High- or low-intensity exercises for strengthening thigh muscles are strongly recommended [25]. Although other studies have focused only on strengthening thigh muscles [8, 11, 18, 20], we chose an overall treatment because of the pathophysiology of knee OA [26] and because there is strong evidence that associating knee exercise and training of proximal and distal muscles to this joint is effective in patients with knee pain [27, 28]. The detailed exercise protocol is shown in Table 2.

**Table 2 Tab2:** Treatment protocol performed by the high-intensity resistance exercise group and blood flow restriction exercise group (adapted from Bryk et al. [15], 2016)

High-intensity resistance exercise group	
- Hamstring stretching, three repetitions of 30 s	
- Bridge with isometric contraction of the transversus abdominis, CORE training, three repetitions of 30 s ^+^	
- Hip abduction with weights (lying on side), three sets of 10 repetitions ^+^	
- Calm exercises (lying on side) with elastic band, three sets of 10 repetitions ^+^	
- Calf raises, three sets of 10 repetitions ^+^	
- Sensori-motor training (standing) on a mini-trampoline, three repetitions of 30 s	
- Squats on a hack machine, 0°–60° of knee flexion, three sets of eight repetitions *	
- Seated knee extensions (machine), 90°–45° of knee flexion, three sets of eight repetitions *	
Blood flow restriction exercise group	
- Hamstring stretching, three repetitions of 30 s	

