- Bridge with isometric contraction of the transversus abdominis, CORE training, three repetitions of 30 s ^+^	
- Hip abduction with weights (lying on side), three sets of 10 repetitions ^+^	
- Calm exercises (lying on side) with elastic band, three sets of 10 repetitions ^+^	
- Calf raises, three sets of 10 repetitions ^+^	
- Sensori-motor training (standing) on a mini-trampoline, three repetitions of 30 s	
- Squats on a hack machine, 0°–60° of knee flexion, one set of 30 repetitions and three sets of 15 repetitions ^‡^	
- Seated knee extensions (machine), 90°–45° of knee flexion, one set of 30 repetitions and three sets of 15 repetitions ^‡^	

The interval between sets will be 30 s and between exercises will be 2 min

*Load is 60% of the 1-repetition maximum

^+^The load will be adjusted every 3 weeks to maintain an effort perception between 6 and 7 on the Borg scale

^‡^Load is 10% of the 1-repetition maximum

Loads of 10% and 60% 1-RM in the BFR exercise and HIRE groups, respectively, will be estimated (1-RM estimated) from the maximum load that can be overcome in 7–10 repetitions (7–10 RM test) [20] based on the Brzycki equation, (W/(1.0278–0.0278 × R), where W refers to weight used in the repetitions until failure and R refers to repetitions to failure [29, 30]. The load will be readjusted every 3 weeks with a 2- to 4-day interval after the last treatment session to prevent residual exercise fatigue from interfering with the 7–10 RM test. Five minutes of warm-up will be performed on a stationary bike before the 7–10 RM test [20, 31]. In relation to the 1-RM test, the 7–10 RM test has the advantage of minimizing the effect of pain on maximum force generation [20].

Participants will be advised that knee pain or discomfort during exercise is normal and that this does not necessarily cause joint damage [9]. All exercises should be performed with pain levels between 0 and 5 on the visual analog scale (VAS) defined as acceptable pain. The session will be interrupted if the patient reports pain greater than 5 or is unable to complete the exercise [23]. The load will be reduced by 20% (relative to 60% of estimated 1-RM) in the HIRE group if the pain prevents the volunteers from completing the exercise [20].

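### A trial sized for non-inferiority names intention-to-treat as its only analysis set, so departures from assigned treatment could help it to conclude similarity

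*Protocol article*

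**What the plan says.** **Aim and sizing.** Sample size estimates (Protocol article) uses "a non-inferiority limit (d) of 14" per cent and "an intergroup variability (σ) in the VAS gain of 21% for both groups", with 5% type-I error, 80% power and 15% dropout, and arrives at 32 per group. The Abstract and the Discussion frame the hoped-for result as similar effects in the two groups.

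**Analysis set.** Statistical analyses states: "All participants will be included in the analysis following an intention-to-treat approach". Study design and Inclusion and exclusion criteria also name ITT, and the Discussion cites it as a mark of quality. The article names no other set.

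**Routes off assigned treatment.** Inclusion and exclusion criteria lists grounds that arise after randomization. One is pain: "Participants will be excluded if they:experience pain that completely prevents them from performing the exercises proposed by two consecutive or three non-consecutive sessions". The others are refusal to continue, new medication for osteoarthritis or affecting the outcomes, and a third rule: "begin to exercise or perform other treatment modalities for knee OA after initiating treatment". The same section then invites those who discontinue to the 3- and 6-month assessments and keeps everyone in the ITT analysis.

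**Comparator load.** Intervention provides, where pain prevents completion: "The load will be reduced by 20% (relative to 60% of estimated 1-RM) in the HIRE group".

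**After week 12.** Intervention says that participants "from then on will be guided to practice exercises according to their own volition".

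**The concern.** In a superiority trial, keeping patients who left their assigned treatment in their randomized arm usually works against the claim. In a non-inferiority trial it can work for it. If patients in both arms stop the exercises or turn to the same outside treatments, their outcomes carry less of the contrast between the regimens, and the observed difference can shrink towards zero.

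This trial has reason to expect departures. It lists specific routes off treatment and budgets 15% dropout. Its Background says that high loads can aggravate pain and reduce adherence. A finding that the very-low-load regimen is not inferior could then partly reflect incomplete delivery of either regimen, and ITT alone would not show whether it did.

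**Working it through.** **Inputs.** Margin 14, SD 21, power 80% and dropout 15% come from Sample size estimates. Sidedness of alpha is not stated there. Only the ratio of margin to SD matters below, so it makes no difference whether the percentages are read as millimetres on the 100-mm scale.

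**Step 1: reproduce the plan's figure.** With a true difference of zero, n per group = 2(z₁₋α + z₀.₈₀)²(SD/margin)².

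- One-sided 5%: 2 × (1.645 + 0.842)² × (21/14)² = 27.8, so 28. Dropout: 27.82 × 1.15 = 31.99, so 32; or 28/0.85 = 32.9, so 33. The stated 32 reproduces.
- One-sided 2.5%: 35.3, so 36, and 36/0.85 gives 43. This does not reproduce.

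The plan was therefore sized for non-inferiority at one-sided 5%. Statistical analyses, however, reports a 95% interval, which corresponds to one-sided 2.5%. Both criteria are carried forward.

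**Step 2: what departures do to the ITT difference.** Suppose a share f of each arm departs, the full-adherence deficit is 14, and the between-arm difference among departing patients is δ. Then

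ITT difference = 14(1 − f) + δf.

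With δ = 0 (assumption: no between-arm difference once off treatment), f = 15% gives 11.9 and f = 25% gives 10.5. With δ = 14 there is no dilution. With δ above 14 the ITT difference exceeds 14 and non-inferiority becomes harder to show.

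**Step 3: chance of declaring non-inferiority when δ = 0.** This is Φ(14f/SE − z₁₋α), with SE = 21√(2/n). Two sizes are used: 32 × 0.85 = 27 per arm and, because the article also gives a total of 40, 20 × 0.85 = 17 per arm (assuming 1:1 allocation). The SEs are 5.72 and 7.20.

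| n per arm | Criterion | f = 0 | f = 15% | f = 25% |
|---|---|---|---|---|
| 27 | one-sided 5% | 5% | about 10% | about 15% |
| 27 | 95% CI | 2.5% | 5.6% | 8.9% |
| 17 | one-sided 5% | 5% | about 9% | about 12% |
| 17 | 95% CI | 2.5% | 4.8% | 7.0% |

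Example: 27 per arm, f = 15%, one-sided 5%: Φ(2.1/5.72 − 1.645) = Φ(−1.28) = 0.10.

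If every randomized patient is retained, as ITT intends, f = 15% gives 10.7% (32 per arm) and 9.2% (20 per arm) at one-sided 5%, and 5.9% and 5.0% on the 95% CI.

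**Step 4: the load reduction.** Where applied, it takes the HIRE load from 60% to 0.6 × 0.8 = 48% of 1-RM, and volume per exercise from 14.4 to 0.48 × 24 = 11.52 times 1-RM, against 7.5 in the BFR group. This narrows the contrast in delivered volume. It does so inside the HIRE regimen as the article defines it, so it is kept apart from the departures above.

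**The case against.** The strongest reply is that this is an omission in a condensed article. A per-protocol definition may sit in an analysis plan that is not shown, and ITT is not itself wrong. That stands in part: nobody can say from the article that no second analysis exists. But the article does fix its analysis set, and it presents ITT as a strength of a trial that seeks similarity. The text as published leaves that conclusion open to dilution.

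The figures also deserve caution. The shares of 15% and 25% are assumptions; the first merely equals the dropout allowance. The error is false relative to the effect under full adherence. For the effect that ITT itself targets, the error rate stays nominal. Statistical analyses describes a test of differences and does not tie the interval to the margin, so the non-inferiority aim is taken from the sample size section and the stated hope of similarity.

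A reader might infer four stronger things that the documents do not support:

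- **That the plan is certain to be biased towards similarity.** If more HIRE patients leave because of pain and then gain from other treatment, HIRE outcomes improve and BFR looks worse. Easing the load for patients in pain could act the same way. No rates or outcomes by arm are given.
- **That the HIRE load reduction is a departure.** It is part of the assigned regimen, so patients under it are treated as assigned. A set requiring the full load would select on pain, the primary outcome domain, in one arm only.
- **That excluded patients drop out of the analysis.** The same section invites those who discontinue to later assessments and keeps everyone in ITT. What remains is loose wording.
- **That the rule against starting exercise threatens the primary result.** The primary outcome is taken after 12 weeks of treatment, and free exercise begins only after that re-evaluation. The natural reading confines the rule to the treatment period.

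**Conclusion.** The point holds as a limit on what the trial can conclude. Relying on ITT alone leaves a non-inferiority finding open to dilution by patients who stop the exercises, start new medication or take up other treatment. Under proportional dilution, with no between-arm difference among departing patients, a 15% share roughly doubles the chance of wrongly declaring non-inferiority: from 5% to about 10% at one-sided 5%, or from 2.5% to about 5.6% on the 95% CI, with 27 per arm. These are illustrations and not predictions; the direction is a risk, and the actual share is unknown. The wording on exclusion and on exercise after week 12 is a secondary matter and does not affect the primary comparison.

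**What to change.** 1. Keep ITT as the main analysis.
2. Prespecify a supportive per-protocol analysis, defined by session attendance and by absence of new osteoarthritis medication or other treatment. Justify the attendance threshold. Recruitment was already under way at submission (Trial status), so fix the rules before outcome data are seen.
3. Count HIRE patients whose load was reduced under the Intervention section as treated as assigned, and report delivered load by arm so that readers can judge the strength of the comparator.
4. State that a non-inferiority conclusion needs the two analyses to be consistent. Discuss any discrepancy, together with the selection bias that a per-protocol set can carry. Whether both must formally meet the margin is debatable and is not required here.
5. In Inclusion and exclusion criteria, say that being excluded after randomization means stopping assigned treatment, with outcomes still collected and analysed.
6. Reconcile the open-ended rule on starting exercise in that section with the free exercise after week 12 in Intervention.

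**Cost.** Some wording, one extra analysis and a slightly harder claim. The percentage of sessions completed is already an outcome; delivered load needs to be logged per session if it is not already.
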